**3.3. Randomization**

Eligible patients who fulfil the inclusion criteria will be randomly assigned to one of the three study arms. Randomization will be stratified for sites and for 3 subgroups according to the renal substitutive therapy (non-dialysis, on haemodialysis, or on peritoneal dialysis), in a 1:1:1 allocation ratio, using a computer-generated randomization list integrated into the Research Electronic Data Capture (REDCap) platform.

- **3HR arm (control).** Consists of three months of daily isoniazid (5 mg/Kg) plus rifampin (10 mg/Kg).
- **3HP arm (experimental 1).** Consists of three months of once-weekly isoniazid (15 mg/Kg) plus rifapentine (900 mg for ≥50 Kgs or 750 mg for 32 to 50 Kgs).
- **4R arm (experimental 2).** Consists of four months of rifampicin (10 mg/Kg).

**3.4. Description of the treatment** (for detailed information, see **Section 5** **“TRIAL INTERVENTION” section**)

- **Isoniazid**

Isoniazid is the hydrazide of isonicotinic acid and is one of the primary drugs for tuberculosis treatment. The activity of isoniazid is limited to the mycobacteria of the *M. tuberculosis* complex. It is bactericidal for rapidly dividing organisms and bacteriostatic for “resting” bacilli. The mechanism of action is the inhibition of the biosynthesis of mycolic acids, a component of the mycobacterial cell wall. It is approved in Spain for the treatment of active and latent TB.

Isoniazid will be part of two arms of the study: in combination with rifampicin (control arm) and combined with rifapentine (experimental 1 arm). In the control arm, participants will receive 5 mg/Kg (up to 300 mg) of isoniazid, administered daily, for three months (90 doses). In the experimental 1 arm, participants will receive isoniazid 900 mg weekly, combined with rifapentine, for 12 weeks.

- **Rifampicin**

Rifampicin is a semi-synthetic rifamycin derivative that is highly active against mycobacteria, most gram-positive bacteria, and some gram-negative bacteria. It is bactericidal for both intracellular and extracellular microorganisms. By inhibiting prokaryotic DNA-dependent RNA polymerase, it suppresses the early elongation of the nucleotide chain in RNA synthesis.

Rifampicin will be part of two arms of the study: in combination with isoniazid (control arm) and as monotherapy (experimental 2 arm). In the control arm, participants will receive 10 mg/Kg (up to 600 mg) of rifampicin, administered daily, for three months. In the experimental 2 arm, participants will receive 10 mg/Kg (up to 600 mg) of rifampicin, administered daily, for four months.

- **Rifapentine**

Rifapentine is a long-acting, cyclopentyl-substituted derivative of rifamycin used to treat mycobacterium infections. It has a role as an antitubercular agent and a leprostatic drug.

Rifapentine will be administered in one of the three study arms (experimental 1 arm). Participants will receive 15 mg/Kg (up to 900 mg) of rifapentine weekly, for 12 weeks, in combination with isoniazid 900 mg weekly, for 12 weeks.

**3.5. Data recorded from participants**

The master file will contain each of the documents required in the guidelines for Good Clinical Practice (CPMH/ICH/135/95). The trial staff will ensure that the participants’ anonymity is maintained. The participants will be identified only by a participant ID number on the Case Report Form (CRF) and any electronic database. All documents will be stored securely and only accessible by trial staff and authorized personnel.

CRF will include demographic data and medical history. If needed be see attachment 2 “Schedule of events” for the complementary tests needed.

**3.6. End of the trial**

The end of the trial is defined as the date of the last visit of the last participant.

**4. SELECTION AND WITHDRAWAL OF PARTICIPANTS**

**4.1. Inclusion criteria**

- Patients 18 years or older with kidney disease stage 5 (glomerular filtrate rate <15 mL/minute or under substitutive renal therapy) who require treatment for latent tuberculosis infection
- Male, or female with negative pregnancy test prior to enrolment
- Female of childbearing age willing to take appropriate barrier contraceptive measures or to abstain from heterosexual intercourse during the study therapy
- Informed written consent

**4.2. Exclusion criteria**

- Prior allergy/intolerance to rifamycins or isoniazid
- Pregnancy or breastfeeding
- Pre-treatment transaminases (ALT and/or AST) >5-fold of the upper limit of the normality
- Concomitant treatment with drugs contraindicated with the study medications
- Having received rifamycins or isoniazid within the two previous weeks
- Weigh <32 Kgs
- Inability to understand the nature of the study or to give written consent

**4.3. Participant withdrawal criteria**

Each participant has the right to withdraw study at any time. In addition, the investigator may discontinue a participant from the study at any time if they consider it necessary for any reason including:

- An adverse event that requires discontinuation of the study medication, mainly liver toxicity caused by isoniazid or rifamycins.
- Non-attendance at two consecutive visits, if it was not because of death.
- Not completing the assigned treatment, for any reason, within the scheduled frame-time (1. not completion of 90 doses within a maximum of 16 weeks, without interruptions longer than 2 weeks, and no more than on 2 occasions, for the 3HR arm [control]; 2. not completing 12 doses within a maximum of 14 weeks, without interruptions longer than 10 days, for the 3HP arm [experimental 1] , and 3. Not completion of 120 doses within a maximum of 20 weeks, without interruptions longer than 2 weeks, and no more than on two occasions, for the 4R arm [experimental arm 2]).

**4.4. Follow-up of participants withdrawn from the trial**

Participants withdrawn from the study because of adverse events will be followed up for four weeks beyond the withdrawal.

**5. TRIAL INTERVENTION**

**5.1. Description of the intervention**

- **Treatment of latent TB infection in the three study arms**
- **3HR arm (control).** Treatment will consist of daily, self-administered, 5 mg/Kg (up to 300 mg) of isoniazid plus daily 10 mg/Kg of rifampin (up to 600 mg), for three months.

Participants will receive one tablet of Cemidon® (isoniazid 300 mg/pyridoxine hydrochloride 50 mg) *(Attachment 1a)*, given on an empty stomach, plus two tablets of Rifaldin® (rifampicin 300 mg) *(Attachment 1b)* or Rimactán® (rifampicin 300 mg) *(Attachment 1c)*, given on an empty stomach. In patients under renal replacement therapy with haemodialysis, Cemidon® and Rifaldin®/ Rimactán® will be administered within two hours after finishing the dialysis session, and at the same hour the non-dialysis days. The total amount of doses taken per patient will be 90.

- **3HP arm (experimental 1).** Treatment will consist of once weekly, self-administered with phone call reminder, 15 mg/Kg (up to 900 mg) of isoniazid, plus rifapentine (900 mg for ≥50 Kgs or 750 mg for 32 to 50 Kgs), for three months.

Participants will receive three once-weekly tablets of Cemidon® (isoniazid 300 mg/pyridoxine hydrochloride 50 mg), given on an empty stomach, plus six once-weekly tablets of Priftin® (rifapentine 150 mg) *(Attachment 1d)*, given with meals. In patients under renal replacement therapy with haemodialysis, both Cemidon® and Priftin® will be administered within two hours after finishing the dialysis session, and at the same hour the non-dialysis days. The total amount of doses taken per patient will be 12.

- **4R arm (experimental 2).** Treatment will consist of self-administered daily 10 mg/Kg (up to 600 mg) of rifampicin, for four months.

Participants will receive two once-daily tablets of Rifaldin® (rifampicin 300 mg) or Rimactán® (rifampicin 300 mg), on an empty stomach. The total amount of doses taken per patient will be 120.

- **Participant’s assessment and follow-up visits**

Listed below are protocol-specified study visits for all recruited subjects *(see attachment 2 for detailed information)*:

- **Enrolment visit.** It will take place within two weeks before starting the study treatment. At this visit, patients will undergo a complete clinical assessment and review of the treatment. Active TB will have already been ruled out by clinical and radiographic assessment.

A blood sample will be obtained in a subset of 100 participants at the coordinator site (Bellvitge University Hospital), for a sub-study on polymorphisms of the N-acetyltransferase (NAT)-2, to determine the acetylator profile (slow/rapid).

- **Allocation visit.** It will be the day 0 visit. Once the written informed consent has been signed, the investigator will proceed to randomize the participant.
- **On-treatment visits.** Participants will undergo follow-up visits while on treatment at days 15, 30, 60 and 90 for the 3HR (control) and the 3HP (experimental 1) arms, and 15, 30, 60, 90 and 120 for the 4R (experimental 2) arm. Adverse events, concomitant medication, and adherence will be assessed by means of a clinical interview at each visit, and blood tests at days 30, 60 and 90 for 3HR (control) and 3HP (experimental 1) arms, or 15, 60 and 120 for the 4R (experimental 2) arm.
- **Close-out visit.** In all the three arms, participants will be assessed 4 weeks after finishing the assigned treatment, at day 120 for the 3HR (control) and 3HP (experimental 1) arms, and day 150 for the 4R (experimental 2) arm.

Visits will be face-to-face at days 30, 60 and 90 for 3HR (control) and 3HP (experimental 1) arms, or 30, 60 and 120 for the 4R (experimental 2) arm. For the 4R arm, the visit at day 90 will be also performed by a phone call. Fifteen-day and post-treatment visits will be done by means of video- or telephone-call, whenever the investigator deems it is safe, and the participant agrees.

- **Monitoring treatment compliance**

Compliance with treatment will be monitored by clinical interview, counting leftover tablets. Assessment of urine colour (orange colour caused by rifampicin) will be carried out on participants with residual diuresis at each face-to-face visit.

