The ESKD patients constitute a fragile population, with frequent intercurrent clinical events, polypharmacy, which often make latent TB difficult to treat, mainly because of adverse events. Data from the TB Unit of the Bellvitge University Hospital with 387 ESKD patients treated with 3HR, 6-9H or 4R prior kidney transplant, showed that 88% completed treatment satisfactorily, and adverse events were the commonest cause of permanent discontinuation (5). Central nervous system toxicity caused by INH is of particular concern in these patients (6-8). Seizures, encephalopathy, dizziness, and cerebellar syndrome have been reported. In our own experience, 9% of patients treated with regimens including INH presented dizziness, referred to as feeling “drunk”. In all the cases, it was invalidating, and improved in a few days after discontinuing treatment. Neurotoxicity has been related to the inhibition of the pyridoxin phosphorylation to the active metabolite, the pyridoxal 5-phosphate. In patients with ESKD, and particularly those under substitutive renal therapy, accumulation of INH metabolites along with the pyridoxal 5-phosphate removal by dialysis, lead to neurotoxicity. In addition, polymorphisms of the N-acetyltransferase (NAT)-2 *2, *5, *6, *7 and *14 alleles, which confer the slow- acetylator phenotype, would contribute to increasing levels of INH and its metabolites, and risk of neurotoxicity (9).

The short-course rifampicin-containing regimens, with or without INH, are currently recommended as the first line treatment for latent TB infection. The combination of weekly rifapentine (RPT) and INH, under supervised administration for 3 months (3HP), has been shown to be no-inferior to the 9H regimen (10), and has already been approved for the first-line treatment of latent TB infection in the USA (11). A metanalysis showed that 87.5% of subjects treated with the 3HP regimen completed treatment, as compared with 65.9% of those treated with INH- or RMP-containing regimens (12). However, the available evidence in ESKD patients is limited to a small number of cases reported in the literature (13-15). A retrospective study with 153 candidates to kidney transplant with latent TB, 93% of the 43 3HP-treated patients and 47% among the 110 treated with the INH for 9 months completed treatment (13). In another two studies, including 17 and 12 transplant candidates treated with 3HP, completion rates were 76% and 100% respectively (14, 15).

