**5.4. Discontinuation of study drugs due to adverse events**

Certain events or conditions may necessitate temporary discontinuation of the study medications. Patients who experience such events or conditions, however, will still be "on study" and will be followed until study completion. Any patient for whom the study medication is temporarily discontinued will be restarted on study medication as soon as possible. If study drugs are definitively discontinued, alternative therapy for latent TB may be administered at the investigator's discretion.

- **Temporary Discontinuation**

Criteria for temporary discontinuation of the study medication:

- Development of a toxicity that, depending on its nature and severity, requires discontinuation of the study medication until the toxicity resolves as indicated in the preceding toxicity management section.
- Development of another medical condition that makes the administration of the study drug inadvisable. The decision to temporarily discontinue the study medication in this situation will be at the investigator's discretion. The period during which the patient is off study medication will be as short as clinically possible.
- **Definitive Discontinuation**

Criteria for definitive discontinuation of study therapy:

- Development of a toxicity that warrants definitive discontinuation of any study medications.
- The patient refuses further study therapy. If a patient refuses further study medication, they will be treated with a non-study regimen, and there will only be a post-treatment visit, four weeks after discontinuing the treatment.
- In the investigator's judgment, continuation of the medication is no longer in the best interest of the patient.
- Liver toxicity: ALT and/or AST elevation >5-fold of the upper limit of the normality or clinical hepatitis during treatment for latent TB infection with one of the IMPs.
- Neurotoxicity: Encephalopathy, dizziness, or cerebellar syndrome during treatment with INH-including regimens. It is commonly referred to as feeling “drunk”. It is usually invalidating and improved after discontinuing treatment.

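### Section 5.1 contradicts itself on 3HP doses below 50 kg: the tablet counts give every participant 900 mg of rifapentine and of isoniazid, whatever the weight-based doses require

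*Protocol*

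**What the plan says.** Section 5.1 of the protocol describes the 3HP arm in two consecutive paragraphs.

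- The first gives the weekly dose by weight: "15 mg/Kg (up to 900 mg) of isoniazid, plus rifapentine (900 mg for ≥50 Kgs or 750 mg for 32 to 50 Kgs").
- The second gives the tablets: "Participants will receive three once-weekly tablets of Cemidon® (isoniazid 300 mg/pyridoxine hydrochloride 50 mg"), "plus six once-weekly tablets of Priftin® (rifapentine 150 mg"). It sets no weight condition.

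Section 4.2 excludes only people weighing less than 32 kg, so the 32 to 50 kg band is part of the trial population.

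Two earlier sections also state 3HP doses:

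- Section 3.3 repeats the weight bands: "rifapentine (900 mg for ≥50 Kgs or 750 mg for 32 to 50 Kgs"), with isoniazid at 15 mg/kg.
- Section 3.4 differs on both drugs. For isoniazid, "participants will receive isoniazid 900 mg weekly, combined with rifapentine, for 12 weeks". For rifapentine, "Participants will receive 15 mg/Kg (up to 900 mg) of rifapentine weekly, for 12 weeks". Its heading refers the reader to Section 5 for detail.

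**The concern.** The two paragraphs of Section 5.1 prescribe different doses for the same people, and nothing in the protocol says which governs. The tablet paragraph is the one a pharmacy can dispense from directly. If it is followed, lighter 3HP participants receive more of both drugs than the dose rule allows.

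The protocol itself explains why this matters here. On isoniazid, Section 1 says: "Central nervous system toxicity caused by INH is of particular concern in these patients". It also reports disabling dizziness in 9% of the centre's own patients on isoniazid-containing regimens. Section 5.4 lists among the criteria for definitive discontinuation: "Neurotoxicity: Encephalopathy, dizziness, or cerebellar syndrome during treatment with INH-including regimens". A participant who stops for good will normally count as a non-completer in the primary endpoint, and discontinuation for adverse events is a secondary endpoint. The dose is therefore unclear in an arm whose better tolerability is the trial's hypothesis.

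There is also a practical side. The trial is multicentre and treatment is self-administered, so sites could dose the same weight differently. Section 5.1 monitors compliance partly by counting leftover tablets, which requires a known expected count.

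**Working it through.** **Inputs.** Tablet strengths and counts are from Section 5.1: isoniazid 300 mg × 3 and rifapentine 150 mg × 6 per weekly dose. The dose rules are from the same section: isoniazid min(900, 15 × kg) mg; rifapentine 900 mg at ≥50 kg and 750 mg at 32 to 50 kg. The lower weight limit of 32 kg is from Section 4.2. Whole tablets are assumed.

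**What the tablet paragraph delivers.** Isoniazid 3 × 300 = 900 mg; rifapentine 6 × 150 = 900 mg. This matches the rifapentine rule at ≥50 kg and the isoniazid rule at ≥60 kg (900/15 = 60).

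**Rifapentine, 32 to <50 kg.** The rule requires 750/150 = 5 tablets and the text gives 6. The ratio is 900/750 = 1.20, or +20%. Both doses are whole tablets, so rounding cannot explain the difference. Over 12 doses the expected count is 12 × 5 = 60 tablets by the rule and 12 × 6 = 72 by the tablet paragraph.

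**Weekly isoniazid.**

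| Weight | Rule (mg) | Rule in tablets | Excess of 900 mg over rule | mg/kg if 900 mg is given |
|---|---|---|---|---|
| 32 kg | 480 | 1.60 | +420 mg (+87.5%) | 28.1 |
| 40 kg | 600 | 2.00 | +300 mg (+50%) | 22.5 |
| 45 kg | 675 | 2.25 | +225 mg (+33%) | 20.0 |
| 49 kg | 735 | 2.45 | +165 mg (+22%) | 18.4 |
| 50 kg | 750 | 2.50 | +150 mg (+20%) | 18.0 |
| 55 kg | 825 | 2.75 | +75 mg (+9%) | 16.4 |
| 60 kg | 900 | 3.00 | 0 | 15.0 |

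Most of these doses are not whole tablets, so the size of the conflict depends on rounding. The rule in tablets is 15 × kg/300 = kg/20. Rounding up gives 2 tablets at ≤40 kg and 3 above. Rounding to the nearest gives 2 below 50 kg. Rounding down gives fewer than 3 below 60 kg. Three tablets is therefore too many at 40 kg and below under every rule, and up to 50 or 60 kg under the other two.

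**Section 3.4.** Its rifapentine rule of 15 mg/kg gives 600 mg at 40 kg (15 × 40) against 750 mg in Section 5.1, and 825 mg at 55 kg (15 × 55) against 900 mg.

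**Other arms.** In 3HR and 4R the text gives two 300 mg rifampicin tablets. The rule of 10 mg/kg is kg/30 tablets: 1.07 at 32 kg and 1.50 at 45 kg. Two tablets is one too many below 45 kg with rounding to nearest, but right at every eligible weight with rounding up. In 3HR, daily isoniazid at 5 mg/kg is 160 mg at 32 kg, or 160/300 = 0.53 tablet. One tablet is the nearest whole-tablet dose at every eligible weight, so there is no conflict there.

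**The case against.** The strongest reply is that the tablet paragraph illustrates the maximum dose. In all three arms it gives exactly the capped amount (300 mg isoniazid with 600 mg rifampicin, 900 mg with 900 mg, and 600 mg), and it serves to name the product, the strength and how to take it. The weight rule appears in both Sections 3.3 and 5.1, which suggests it is the intended one. This is a plausible account of how the wording arose. It does not remove the conflict, because the paragraph is written as an instruction for all participants and nothing says the weight rule prevails.

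Several narrower objections do stand:

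- The isoniazid conflict is less clear-cut than the rifapentine one. Above 40 kg it depends on a rounding rule that the protocol text does not state. The product data sheets it attaches are not available here.
- Light 3HR participants also exceed their mg/kg rule: 300 mg against 160 mg at 32 kg is the same +87.5%, and it is taken daily. The finding therefore does not show a distortion of the comparison specific to 3HP.
- Each isoniazid tablet carries 50 mg of pyridoxine, so pyridoxine rises with the tablet count.
- Completion is counted in doses within a time window, not in milligrams, so the endpoint definition is untouched. The path from extra dose to neurotoxicity to non-completion is a possibility, not a demonstrated effect.
- The overlap at exactly 50 kg and the mismatch in Section 3.4 are minor. Section 3.4 defers to Section 5.

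**Conclusion.** The concern holds: Section 5.1 is wrong as written and should be fixed. For rifapentine, the tablet count exceeds the stated dose by one tablet (150 mg, +20%) for every 3HP participant of 32 to <50 kg, and no rounding rule reconciles the two. For weekly isoniazid, three tablets is at least one too many at 40 kg and below under any rounding rule, and below 50 kg with rounding to nearest. At 32 kg the participant would take 28.1 mg/kg against a stated 15 mg/kg.

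These figures assume whole tablets of the named strengths. How many participants are affected cannot be computed, because the protocol gives no weight distribution. No size is claimed for any effect on completion or discontinuation. The rifampicin counts, the Section 3.4 doses and the band edge at 50 kg are secondary points to tidy at the same time.

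**What to change.** In Section 5.1, make the 3HP tablet counts conditional on weight: five rifapentine tablets (750 mg) for 32 to <50 kg and six (900 mg) for ≥50 kg. For weekly isoniazid, and for rifampicin in 3HR and 4R, state the whole-tablet rounding rule below 60 kg or an explicit flat dose, confirmed by the clinical and pharmacy leads. Write the lower rifapentine band as 32 to <50 kg in Sections 3.3 and 5.1. Replace the dose statements in Section 3.4 with a reference to Section 5.1.

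The cost is amendment wording and a pharmacy dispensing sheet. If the change is classed as a substantial amendment, Section 9 requires ethics committee and regulatory approval. Sample size and analysis are unaffected.

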**12. ATTACHMENTS**

**Attachment 1a.** Data sheet of Cemidon®

**Attachment 1b.** Data sheet of Rifaldin®

**Attachment 1c.** Data sheet of Rimactán®

**Attachment 1c.** Data sheet of Priftin®

**Attachment 2.** Scheduled assessment visits

**Attachment 3a.** Informed consent form

**Attachment 3b.** Appendix

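### Protocol 5.1 puts the first 4R blood test on day 15, a default-remote visit, and none on the in-person day-30 visit; in 3HR and 3HP test days and in-person days coincide.

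*Protocol*

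**What the plan says.** Three statements in Protocol Section 5.1 bear on this.

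- **Blood tests.** The on-treatment schedule has "blood tests at days 30, 60 and 90 for 3HR (control) and 3HP (experimental 1) arms, or 15, 60 and 120 for the 4R" arm.
- **In-person visits.** "Visits will be face-to-face at days 30, 60 and 90 for 3HR (control) and 3HP (experimental 1) arms, or 30, 60 and 120" for 4R.
- **Remote visits.** "Fifteen-day and post-treatment visits will be done by means of video- or telephone-call, whenever the investigator deems it is safe", and provided the participant agrees. This covers all three arms. A further sentence makes the 4R day-90 visit a telephone call.

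The full list of 4R on-treatment visits is "15, 30, 60, 90 and 120 for the 4R (experimental 2) arm", so day 30 is a scheduled 4R visit.

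For detail, Section 5.1 refers to an attachment ("see attachment 2 for detailed information"). Section 3.5 sends the reader to the same attachment "for the complementary tests needed", and Section 12 lists it as "Scheduled assessment visits". It is not among the pages at hand.

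**The concern.** A blood draw needs the participant to be present. In 4R the first draw is tied to a visit planned as a call, and the in-person visit two weeks later has none. Section 5.1 gives no reason for an early test in 4R alone and does not say how blood is obtained on day 15.

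Two things are at stake. First, consistency between sites: one may call the participant in, another may arrange a separate draw, and a third may move the test to day 30. Haemodialysis participants could perhaps be sampled at a dialysis session, but Section 5.1 does not say so. The randomisation strata in Section 3.3 are "non-dialysis, on haemodialysis, or on peritoneal dialysis", and for the first and last of these Section 5.1 plans no in-person contact on day 15.

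Second, comparability of safety data. Section 5.4 requires permanent discontinuation when ALT or AST exceeds five times the upper limit of normal, Section 7.8 makes liver toxicity an event of special interest, and Section 3.1 makes discontinuation for adverse events a secondary endpoint. In a participant without symptoms, a raised transaminase is found only if blood is taken, so the timing of tests affects when such events can be detected in each arm. Section 5.1 does not list the analytes; that these tests include transaminases is inferred from the stopping rule in Section 5.4.

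**Working it through.** There is no sample size or power figure to reproduce. The check compares the lists of days in Section 5.1.

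| Visit day | 3HR and 3HP: mode | 3HR and 3HP: blood test | 4R: mode | 4R: blood test |
|---|---|---|---|---|
| 15 | remote by default | no | remote by default | **yes** |
| 30 | in person | yes | in person | **no** |
| 60 | in person | yes | in person | yes |
| 90 | in person | yes | telephone | no |
| 120 | close-out, remote by default | none listed | in person | yes |

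**Step 1: overlap of test days and in-person days.**
- 3HR and 3HP: {30, 60, 90} against {30, 60, 90}; overlap 3 of 3.
- 4R: {15, 60, 120} against {30, 60, 120}; overlap {60, 120}, that is 2 of 3.

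**Step 2: is the 4R day-15 entry the only exception?** Yes. Every other listed test falls on an in-person day. Every other remote visit, including the 4R day-90 call, has no listed test. The 4R day-30 visit is the only in-person on-treatment visit without one.

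**Step 3: timing against control in the first 60 days.** Control is tested on days 30 and 60, and 4R on days 15 and 60. The number of tests is the same (2 and 2); the day of the first differs by 30 − 15 = 15 days, with 4R earlier as written.

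**Step 4: effect of replacing 15 by 30.** The 4R test days become {30, 60, 120}, equal to the in-person days (3 of 3). The first test is on the same day as in control (30 − 30 = 0) and 15 days later than written. Scheduled gaps between 4R tests, counted from day 0, change from 15, 45 and 60 days to 30, 30 and 60 days. The total stays at three.

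**The case against.** The strongest reply is that nothing here is strictly contradictory. Section 5.1 does not restrict blood draws to in-person visits, and the call on day 15 is conditional. An investigator who needs blood that day can see the participant without departing from the text. Followed literally, 4R has as many on-treatment tests as the other arms and an earlier first one. Adverse events are also asked about at every visit, and the stopping rule in Section 5.4 acts on clinical hepatitis as well as on transaminases. Attachment 2 may already give sites the intended day.

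Most of this stands, and it limits the point. It does not remove it: the section still ties a test to a default-remote visit in one arm only, without saying how it is to be done. If Attachment 2 gives day 30, it conflicts with Section 5.1. If it gives day 15, Section 5.1 still needs to say how blood is drawn.

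Three stronger readings are tempting, and the protocol supports none of them.

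- *That 4R participants will go untested until day 60.* This needs the day-15 draw to be skipped and also not recovered at the in-person day-30 visit. Nothing shows how often that would happen, so no number of missed tests and no length of delay can be given.
- *That 15 is a proven slip for 30.* The pattern across arms suggests it, but the intended day is not stated.
- *That the comparison of treatment completion is biased.* No effect on the primary endpoint can be derived from this schedule.

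**Conclusion.** The point holds as a conflict in the operative 4R visit schedule. One of the three 4R blood tests, the first, sits on a visit that is remote by default, against none of three in 3HR and 3HP. It applies to all planned 4R participants (75, Section 8.2). As written, the first laboratory check comes at a different time in 4R and control, and sites have no instruction on how to carry it out, so laboratory detection of liver toxicity in the first two months is not aligned between arms.

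The mismatch between the lists is certain from the text. Two things are assumed: that the tests include transaminases, and that day 30 is the intended day. The second should be confirmed before the text is changed. The correction is worth making because it concerns safety monitoring and is cheap, but sites could work around the conflict.

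**What to change.** Check Attachment 2 and confirm the intended day. Unless day 15 is deliberate, change the 4R blood-test days in Section 5.1 from 15, 60 and 120 to 30, 60 and 120, and make Attachment 2 agree.

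This costs one number in the text. It adds no visit and no test, because 4R already has an in-person visit on day 30. The small downside is a first 4R test 15 days later than now written.

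If day 15 is deliberate, keep it, give the reason, and state either that the 4R day-15 visit is in person or how blood is to be drawn that day when the visit is a call. Making it in person raises planned 4R in-person on-treatment visits from 3 to 4 per participant, at most 75 × 1 = 75 extra visits in all.
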